### Study population

The study population is community-dwelling older adults with mild-to-moderate AD. The inclusion and exclusion criteria for the study sample are detailed in Table 1. Mild-to-moderate AD will be defined as Clinical Dementia Rating (CDR) scores of 0.5 to 2 and Mini-Mental State Examination (MMSE) scores of 15 to 26. We will proactively recruit minorities using recommended strategies, such as providing educational seminars and hiring ethnically diverse staff [47].

**Table 1 Tab1:** **Eligibility criteria**

Inclusion criteria:	Exclusion criteria:
a) Verified diagnosis of Alzheimer’s disease	a) Resting heart rate ≤50 or ≥100 beats/minute
b) Mini-Mental State Examination score 15 to 26	b) Neurologic disorders (for example, non-Alzheimer’s dementia or head trauma)
c) Clinical Dementia Rating scale score 0.5 to 2	c) Psychiatric disorders (for example, bipolar, schizophrenia, or major depression)
d) Community-dwelling	d) Alcohol or chemical dependency
e) Age 66 years and older	e) Contraindications to exercise
f) English-speaking	f) If volunteered for Magnetic Resonance Imaging, abnormal imaging findings
g) Verified exercise safety	g) New symptoms or diseases (for example, chest pain, thrombosis) that have not been evaluated by the primary care provider
h) If on Alzheimer’s drugs, stable on drugs more than one month	h) Abnormal findings from the symptom-limited cycle-ergometer test (for example, cardiac ischemia or arrhythmia, inability to cycle)

### Sample size

The primary endpoint is the 6-month within-group change in the ADAS-Cog, compared with the mean increase of 3.2 points from pooled placebo groups in AD drug RCTs with a total sample size of 534 (assuming equal numbers of mild and moderate AD subjects) [48]. Power calculations were based on a one-sample *t-* test (2-sided) at the 0.05 level, using the pooled standard deviation (SD) = 6.25 from the same placebo groups in AD drug RCTs [48]. Sample size was further determined by factoring in 16% attrition, which was based on the attrition rates from our previous studies [19, 20], 12 to 41% attritions in AD drug RCTs [49], and 0 to 41% attritions in non-AD exercise RCTs [12]. As a result, we will enroll 90 subjects and randomize 60 to the cycling group and 30 to the control group. The power calculation is conservative as it does not account for the stratified randomized design (or equivalently assumes that there is no difference between the strata, see below).

If 50 subjects in the exercise group complete the 6-month measurement, then the study has 80% power to detect a difference of at least 2.5 points with a one-sample 2-sided *t*-test at the 0.05 level. That is, if cycling leads to a true mean increase in the ADAS-Cog of no more than 0.7 points, the study will have 80% power to detect a difference from the increase of 3.2 observed in placebo groups in AD drug RCTs. In our control group, if 25 complete the trial, then the expected half-width of the 95% confidence interval for the mean 6-month change in the control group is 2.4. Although there is little power to detect a difference between our controls and the placebo groups in AD drug RCTs, our trial will provide a valuable estimate of the intervention’s Hawthorne effect.

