#### Randomization, allocation concealment, and blinding

Randomization will allocate subjects 2:1 (cycling: stretching) within each age stratum (66 to 75, 76 to 85, and 85+), and will use randomly permutated blocks of 3 and 6 subjects (Figure 1). We do not expect equal numbers of subjects in each age stratum, but want to ensure that the two randomized groups are balanced across each age stratum. Because the effect of the intervention may vary across age strata similar to varying AD prevalence across age groups [50], this design will reduce the variability in the comparisons within and between randomized groups.

Allocation is concealed from all investigators except for the statistician. Study staff will not be blinded. Enrolled subjects will be randomized after completing baseline data collection.

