#### Aim 1: determine the immediate effect of the cycling intervention on cognition in Alzheimer’s disease

The primary comparison for both hypotheses in Aim I will be a 2-sided test of the overall mean in a 1-way ANOVA with age stratum as the factor and the change in ADAS-Cog from baseline to 6 months as the response against the null hypothesis value of 3.2 points, which is the mean 6-month increase in ADAS-Cog in pooled placebo groups of AD drug RCTs (n = 534) [48]. Separate ANOVAs will be run for each randomization group. Because we stratified treatment assignment (by age) in the design of the study, it is important that we account for this in the analysis of the trial data in order to realize the improved power of this design. Missing values at 6 months will not be imputed by last-observation-carried-forward because this would bias the mean change toward zero. Further analysis will use an analysis of covariance (ANCOVA) to determine significant difference in ADAS-Cog between groups at 6 months after adjusting for other covariates, including baseline ADAS-Cog and age stratum as covariates. Other covariates and potential outcome variables at baseline (Table 4) will be screened for possible inclusion in the model if any are associated with ADAS-Cog at a *P* < .1 level.

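### The primary test and its power treat the historical value of 3.2 as a known constant, without carrying its sampling error or the equal mild/moderate mix it assumes

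*Protocol article*

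**What the plan says.** The Sample size section makes the 6-month within-group change the primary endpoint, "compared with the mean increase of 3.2 points from pooled placebo groups in AD drug RCTs". It then describes that historical source as a pool "with a total sample size of 534 (assuming equal numbers of mild and moderate AD subjects"). Power is computed for a one-sample t-test "using the pooled standard deviation (SD) = 6.25 from the same placebo groups in AD drug RCTs". With 50 cycling completers the section states 80% power for a difference of 2.5 points, that is, a true increase of 0.7 instead of 3.2.

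The Aim 1 analysis tests the overall mean of a one-way ANOVA on age stratum, separately in each arm, "against the null hypothesis value of 3.2 points, which is the mean 6-month increase in ADAS-Cog in pooled placebo groups of AD drug RCTs". It mentions no standard error for 3.2 and no adjustment of 3.2 for disease severity.

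The Study population section and Table 1 admit MMSE 15 to 26 and CDR 0.5 to 2, with no quota for mild or moderate disease. On allocation, "Randomization will allocate subjects 2:1 (cycling: stretching) within each age stratum"; severity is not a stratification factor. The Discussion explains that a historical control was chosen because the comparison between the randomized arms lacks power.

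**The concern.** Two properties of 3.2 are dropped between the Sample size section and the Aim 1 test.

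1. **It is an estimate.** A mean from 534 patients has sampling error. A one-sample test against a constant leaves that error out, so the standard error is too small and the p-value too optimistic.
2. **It depends on a severity mix.** The Sample size section ties 3.2 to equal numbers of mild and moderate patients. If mild and moderate patients change at different rates and the enrolled mix is not 50:50, then 3.2 is not the expected untreated change in this sample. Randomization does not protect against this, because the comparator is external. A mix weighted to slower decliners could give a significant result with no benefit from cycling; the opposite mix could hide a benefit.

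At stake is the interpretation of the primary result, which rests on this one number.

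**Working it through.** **Inputs (all from Sample size):** null value 3.2; SD 6.25; historical N = 534; 50 cycling completers; two-sided α = 0.05; difference 2.5.

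**Step 1. Reproduce the plan's figure.** SE = 6.25/√50 = 0.884 and the noncentrality is 2.5/0.884 = 2.83. The noncentral t with 49 df gives power 79.2%; the normal approximation gives 80.7%. The stated 80% is reproduced for a fixed null. These figures use the one-sample t-test of the power calculation and so ignore the age-stratum factor.

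**Step 2. Sampling error of 3.2.** SE = 6.25/√534 = 0.27, so the 95% interval is 3.2 ± 1.96 × 0.27, or 2.67 to 3.73. This is a lower bound: it treats the 534 as one independent sample, and variation between the pooled trials, which is not given, would enlarge it.

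**Step 3. The planned test, averaged over that error.** Take the error in 3.2 as normal with SD 0.27 and average the rejection probability of the fixed-3.2 test:
- true difference 0: type I error 6.0% (nominal 5%);
- true difference 2.5: average power 78.2%.

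**Step 4. A test that carries the error.** SE = √(6.25²/50 + 6.25²/534) = √(0.781 + 0.073) = 0.924, and the noncentrality is 2.5/0.924 = 2.70.
- Welch, about 58.6 df: power 75.8%.
- Pooled, 582 df: power 77.0%.

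Both hold 5% under the stated inputs. With the pooled test, the difference detectable at 80% power is about 2.59 points, and 80% power for 2.5 points needs 55 completers, or 55/0.84 ≈ 66 randomized to cycling.

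**Step 5. Case mix, by assumption.** If D is the mild/moderate difference in mean 6-month change, the null is off by (mild share − 0.5) × D. The document gives neither D nor the expected share, so the size of the shift is an assumption. With n = 50 and the test against fixed 3.2:

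| Null off by (points) | False rejection, no cycling effect | Power for a true 2.5-point benefit, shift against cycling | Same, shift in favour |
|---|---|---|---|
| 0 (50:50 mix, or D = 0) | 5.0% | 79% | 79% |
| 0.2 | 5.6% | 72% | 85% |
| 0.5 | 8.6% | 60% | 91% |
| 1.0 | 19.9% | 38% | 97% |

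For orientation, 0.2 corresponds to a 70:30 mix with D = 1, and 1.0 to a 75:25 mix with D = 4. Nothing in the document makes one row more likely than another. The table leaves out the sampling error of Steps 2 to 4.

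**The case against.** A reader might infer that the stated power is miscalculated. It is not: 80% follows from the plan's own inputs for the test that the plan names. It is conditional on 3.2 being the true untreated mean.

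A reader might also infer that the plan claims 3.2 is valid for any severity mix. It makes no such claim; the equal-numbers assumption is printed beside the figure. What stands is that the Aim 1 test does not carry that disclosed assumption through.

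Nor should 76% to 77% be read as the power of the planned test. That belongs to the replacement test. The planned test loses about 1 point of power (79.2% to 78.2%) and gains about 1 point of type I error. Testing one arm against a fixed benchmark is a recognized design, this is a pilot, and the Discussion is open about why the historical control was used. Taken alone, the sampling-error part is minor.

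The plan also has partial safeguards. Hypothesis 1b checks the benchmark in concurrently randomized controls. The between-group ANCOVA and the mixed models are not biased by a mix that departs from 50:50, and AD stage is a candidate covariate. These mitigate but do not cure. The control-arm interval has a stated half-width of 2.4 points, and the plan concedes little power there, so a null off by 1 point would normally go unnoticed. The between-group models are further analyses and cannot correct a one-sample null.

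Finally, the large false-rejection rates in the case-mix table rest on shifts that the document does not supply. They cannot be presented as the trial's expected error rate.

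**Conclusion.** The point holds in limited form. The nominal 5% and the stated 80% are conditional on 3.2 being exactly the untreated mean for the patients enrolled.

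- **Sampling error:** established from the plan's own figures, and small. Type I error is about 6.0% and average power about 78% for the planned test; power is about 76% (Welch) to 77% (pooled) once the error is carried. This assumes SD 6.25 in both groups and 534 independent patients, so 0.27 is a minimum.
- **Case mix:** the mechanism is real, because no quota, stratum or adjustment secures the mix on which 3.2 depends. Size and direction are unknown. The effect is zero at 50:50, and 5.6% to 19.9% false rejection is an assumed range for a null off by 0.2 to 1.0 point.

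A correction is worthwhile because this is the primary test and the first part costs almost nothing.

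**What to change.** (a) Test the cycling arm against the historical group with standard error √(s²/n + 6.25²/534), where s and n are the arm's SD and number of completers. Restate power for 2.5 points as about 76% to 77%.

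(b) If the source reports placebo changes by severity, with cut-points that map to this trial's MMSE and CDR ranges, replace 3.2 by the mean of those changes weighted to the enrolled baseline mild/moderate mix. If it does not, prespecify a range of null values and report the primary test across it. In either case, fix the rule before outcomes are linked to allocation, so that the null cannot be chosen after the results are seen.

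**Cost.** Part (a) is a wording change and a few lines of code; stated power falls by about 3 to 4 points. Part (b) uses MMSE and CDR data already collected at screening, but its first option depends on what the source reports, which the document does not show. Reweighting for severity would also leave other differences from the historical trials, such as setting and background treatment, untouched.

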##### Hypothesis 1b

Control subjects will have the same within-group increase in ADAS-Cog at 6 months as placebo subjects in AD drug RCTs.

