#### Stretching exercise

Stretching exercise will not exceed 20% of HR reserve or RPE 8 and will include primarily seated movements and static stretches. Stretching exercise will begin seated with very slow and deliberate calf raises, knee extensions, knee lifts, elbow flexion, shoulder abduction, and shoulder shrugs. Thereafter, stretches will be performed as follows: seated static calf stretch; seated anterior tibialis stretch; seated triceps stretch; seated deltoid stretch; assisted seated pectoralis major stretch; seated trapezius stretch; seated neck lateral rotation (looking over shoulder slowly); seated piriformis stretch; and standing calf stretch using chair for balance. There will be a minimum 2-minute rest between stretches. The number of repetitions and durations for each stretch will be gradually increased to match the session duration of cycling (Table 2).

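### The control arm's change against a drug-trial placebo benchmark cannot estimate a Hawthorne effect, because the two-arm design does not separate attention from what else may differ

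*Protocol article*

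**What the plan says.** The benchmark, given under Sample size, is a "mean increase of 3.2 points from pooled placebo groups in AD drug RCTs with a total sample size of 534", derived by "assuming equal numbers of mild and moderate AD subjects". The "pooled standard deviation (SD) = 6.25 from the same placebo groups in AD drug RCTs" supplies the variability. With 25 control completers the section expects a 95% half-width of 2.4 points for the control arm. It concludes that "our trial will provide a valuable estimate of the intervention’s Hawthorne effect". The only reservation it states is that the trial has small power to tell its controls apart from the drug-trial placebo patients.

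Hypothesis 1b reads: "Control subjects will have the same within-group increase in ADAS-Cog at 6 months as placebo subjects in AD drug RCTs". Under Statistical analyses, Aim 1, it is tested by setting the control arm's mean change against the fixed value 3.2, in a separate ANOVA for that arm with age stratum as the only factor. No adjustment for differences from the benchmark population is described for this test.

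The Design section describes two arms, both exercising in sessions three times a week, with stretching labelled an attention control. There is no low-contact or usual-care arm.

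**The concern.** A Hawthorne effect is a response to being observed and attended to. To estimate it, one needs two groups that differ in attention and in nothing else that moves the outcome. The comparator here is an external number from other trials, and the control arm receives more than attention.

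The label matters because the primary endpoint compares cycling with the same 3.2. Any response to contact and attention is therefore part of the primary result, and the control-versus-3.2 figure is offered as the gauge of that response. If the Hypothesis 1b test is non-significant, which is likely at this sample size even with a real departure of 1 or 2 points, a report using this label could be read as evidence that attention contributes nothing. That would lend the cycling-versus-3.2 result support it has not earned. The trial is also meant to pilot the components of a full-scale trial, so a mislabelled estimate could be carried forward.

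**Working it through.** **1. The protocol's own precision figure.** Inputs from Sample size: SD 6.25, 30 controls, 16% attrition.

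- Completers: 30 × 0.84 = 25.2, which agrees with the 25 used.
- Standard error: 6.25 / √25 = 1.25.
- Normal half-width: 1.96 × 1.25 = 2.45. The stated 2.4 matches this version.
- t half-width, 24 df: 2.064 × 1.25 = 2.58.
- Allowing for sampling error in the benchmark (n = 534): SE = 6.25 × √(1/25 + 1/534) = 1.28, half-width 1.96 × 1.28 = 2.51.

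The figure reproduces, but it describes random error only.

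**2. What the contrast contains.** Write D = (mean control change) − 3.2. Then

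D = A + S + U + P, where

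- A is the effect of attention beyond whatever the benchmark patients received. They were trial participants on placebo; their contact schedule is not given.
- S is any effect of the movement programme. The section on stretching limits its intensity ("Stretching exercise will not exceed 20% of HR reserve or RPE 8") but describes real movements and stretches.
- U is any effect of support: transport, frequent caregiver communication and help with unmet needs (Setting; Table 3).
- P is any difference in population, setting or period. Table 1 admits patients on stable Alzheimer's drugs and screens by exercise safety and a cycle-ergometer test. The benchmark assumes a 50:50 mild-to-moderate mix, while Study population and Table 1 set ranges on the CDR and MMSE and no quota, and randomisation is stratified by age only.

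The trial yields one number, D, for this contrast. No second equation separates A from S, U and P. Increasing n shrinks the standard error of D and leaves S + U + P untouched.

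**3. Power of the Hypothesis 1b test.** One-sample two-sided t-test, n = 25, SD 6.25, level 0.05 (noncentral t):

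| True departure from 3.2 | Power |
|---|---|
| 1 point | 12% |
| 2 points | 34% |
| 2.5 points | 48% |
| 3 points | 63% |
| 3.65 points | 80% |

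**4. Effect of non-attention differences.** The documents give no value for S + U + P, so a range is assumed. Coverage of the true A by the nominal 95% interval (t, n = 25):

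| Assumed S + U + P (either sign) | Coverage |
|---|---|
| 0.5 | 93% |
| 1 | 88% |
| 1.5 | 79% |
| 2 | 66% |
| 2.5 | 52% |

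**5. What the randomised comparison does.** (Cycling change − 3.2) − (control change − 3.2) = cycling change − control change. The benchmark cancels, and so does what the two arms share.

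**The case against.** The best defence is that this is a single closing remark. The Hawthorne effect is not an aim, outcome or planned analysis. Comparing control change with 3.2 is computable and described for what it is, and the low power and interval width are disclosed. The phrase can also be read as the added effect of this programme's contact beyond ordinary trial participation. On that reading observed placebo patients are a sensible reference, and transport and caregiver contact belong to the attention being measured. Most of this stands and limits the severity. It does not rescue the claim, because stretching and possible population differences remain mixed in on either reading.

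Four stronger readings are tempting and are not supported:

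- A reader might infer that the trial will subtract a Hawthorne estimate from the cycling result. No section plans this, and within this trial the subtraction would only return the randomised contrast (step 5).
- A reader might infer that Hypothesis 1b contradicts the promised estimate. Predicting that a quantity is zero and estimating it with an interval are compatible.
- A reader might infer that the control arm is known to differ from the drug-trial patients in eligibility and setting. The article gives only the benchmark's mean, SD, size and severity-mix assumption, so differences are possible but not shown.
- A reader might infer that an apparent effect of 2.5 points could not be distinguished from zero. That holds with the t half-width (2.58), but not with 2.45 or the stated 2.4.

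**Conclusion.** The claim should be withdrawn. It asserts a property that the two-arm design lacks, so it is not a detail that an analysis plan could supply later. The problem is identification, and no corrected figure exists. For scale, random error alone gives a half-width of 2.45 to 2.58 points, about the 2.5-point cycling target, and departures of 1 to 2 points would be detected only 12% to 34% of the time.

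These figures rest on the protocol's SD of 6.25 and 25 completers. The coverage figures rest on assumed biases. That the placebo patients' own trial attention affected their scores is plausible, but the article does not show it.

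This is a minor interpretive error. It bears on how Hypothesis 1b, and through it the cycling-versus-3.2 result, may be read. The between-group ANCOVA and the mixed models stand without it.

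**What to change.** - Delete the Hawthorne claim from Sample size.
- Report the control arm's mean 6-month change with its 95% confidence interval as a descriptive comparison with a historical benchmark. State that its departure from 3.2 may combine attention, stretching, support services, and differences in case mix, background drugs, fitness selection and setting.
- State that a non-significant Hypothesis 1b test will not be taken to show that attention has no effect or that controls change as placebo patients do.
- Rely on the randomised cycling-versus-stretching comparison, already planned under Aims 1 and 2, for effects net of components common to both arms.

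The cost is wording only: no endpoint, test or sample size changes. The downside is that one claimed deliverable is lost.

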### Study procedure

#### Staff training

All staff will be adequately trained by the research team to ensure subject safety, blinding, data quality, and study-protocol adherence. Initial staff training spans three months using a variety of methods including reading, lectures, demonstration, discussions, role plays, practice rounds, and test runs with real subjects. Subsequent training of research assistants (RAs) and volunteers are conducted jointly by staff and the investigators and tailored to the skills needed for a given role. Ongoing training for staff, RAs, and volunteers is provided by the research team through weekly staff meeting, monthly research team meeting, briefing after each treatment fidelity check, and participation in new staff/RA/volunteer training.

#### Randomization, allocation concealment, and blinding

Randomization will allocate subjects 2:1 (cycling: stretching) within each age stratum (66 to 75, 76 to 85, and 85+), and will use randomly permutated blocks of 3 and 6 subjects (Figure 1). We do not expect equal numbers of subjects in each age stratum, but want to ensure that the two randomized groups are balanced across each age stratum. Because the effect of the intervention may vary across age strata similar to varying AD prevalence across age groups [50], this design will reduce the variability in the comparisons within and between randomized groups.

Allocation is concealed from all investigators except for the statistician. Study staff will not be blinded. Enrolled subjects will be randomized after completing baseline data collection.

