**Methods/Design:**

This pilot randomized controlled trial will investigate the effects of a 6-month, individualized, moderate-intensity cycling intervention (20 to 50 minutes per session, 3 times a week) on cognition and hippocampal volume in community-dwelling older adults with mild-to-moderate Alzheimer’s disease. The specific aims are to: 1) determine the immediate effect of the cycling intervention on cognition in Alzheimer’s disease; 2) examine if the cycling intervention slows cognitive decline in Alzheimer’s disease from baseline to 12 months; and 3) assess the effect of aerobic exercise on hippocampal volume over 12 months. Ninety subjects will be randomized on a 2:1 allocation ratio to cycling or attention control (low-intensity stretching) and followed for another 6 months. Allocations will be concealed to all investigators and outcome assessors will be blinded to group assignments and previous data. Cognition will be measured by the Alzheimer’s disease Assessment Scale-Cognition at baseline before randomization and at 3, 6, 9, and 12 months. Hippocampal volume will be measured by magnetic resonance imaging at baseline and 6 and 12 months. The sample size of 90 will give 80% power to detect a 2.5-point difference in within-group changes in the Alzheimer’s disease Assessment Scale-Cognition at 6 months for the cycling group.

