#### Recruitment, screening, and enrollment

This study recruits in a Midwestern state of the United States. We will recruit using a variety of strategies such as referrals by local Alzheimer’s Association chapter, medical centers, and health care providers, study presentations, advertisement, websites, conference exhibits, and press release. Ninety subjects will be enrolled over a 5-year period using the inclusion/exclusion criteria (Table 1). Respondents to our recruitment will undergo a 4-step screening process to qualify for the non-MRI part of the study:Phone screen (5 to 10 minutes) to elicit AD diagnosis and contraindications to exercise;In-person interview (2 hours) at the CTSI to obtain informed consent/assent and Health Insurance Portability and Accountability Act (HIPAA) and medical record release authorization. Then, two staff will take turns to interview the subject and family caregiver separately. For example, an RA will first interview the subject using the MMSE and health history form, while the study coordinator will interview the family caregiver using the CDR. Afterwards, the RA will interview the caregiver using the health history form, while the study coordinator will interview the subject using the CDR and conduct a focused neurologic and cardiac physical exam;Medical verification of AD diagnosis, exercise safety, and MRI safety with the subject’s health care providers (1 to 4 weeks). Medical verification letter will be sent if the subject’s CDR is 0.5 to 2 and MMSE is 15 to 26; andSymptom-limited peak cycle-ergometer test (30 to 60 minutes) to rule out cardiac ischemia and serious arrhythmia and determine peak heart rate (HR) and maximal oxygen consumption (VO_2peak_). The test is conducted either by a trained exercise technician, a study staff/RA, and a physician co-investigator, or a trained exercise technician, a study staff/RA, and an allied health professional trained in supervising exercise testing with the physician on call.

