**Subject flow and timeline.**

#### Data collection

Enrolled subjects will be scheduled to complete baseline data collection (about 3 hours). Subsequent data collection will occur at 3, 6, 9, and 12 months for cognition and other outcomes, which are further described under ‘Variables and Their Measures’ and in Figure 2. Subjects who undergo MRI at baseline will be re-evaluated for eligibility for MRI at 6 and 12 months (Figure 2). The first five data collections will be double checked by co-investigators and serve as further training for data collectors. Data collected by one assessor will be separately scored and entered into the study database by another assessor. Data collectors will not interact with enrolled subjects except for data collections.

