#### Treatment fidelity

This study was designed to ensure treatment fidelity based on the National Institutes of Health Behavioral Change Consortium recommendations [52]. The co-investigators such as the exercise physiologist will assess treatment fidelity on all session case reports via weekly meeting with the exercise interventionist and conduct in-person fidelity check in 2% of randomly selected exercise sessions using a standard form. The exercise interventionist will be re-trained as needed.

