#### Data audits

Data audits of electronic outcome data will be conducted by the PI. If the PI identifies any discrepancies in scoring between the RA who collected data and the RA who entered data, the RAs need to consult the neuropsychologist co-investigator for correct scoring and the correct scores will be documented on paper and entered into REDCap.

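### Allocation is said to be concealed from every investigator but the statistician, yet co-investigators review all session reports and so know the arm; nothing else protects those who audit or decide outcome scores

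*Protocol article*

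**What the plan says.** On who knows the allocation, the section on randomization, allocation concealment and blinding says: "Allocation is concealed from all investigators except for the statistician. Study staff will not be blinded". The abstract (Methods/Design) is broader still: "Allocations will be concealed to all investigators and outcome assessors will be blinded to group assignments and previous data". The Design section adds that data collectors are blinded.

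On who sees the exercise data, the Treatment fidelity section says: "The co-investigators such as the exercise physiologist will assess treatment fidelity on all session case reports via weekly meeting with the exercise interventionist". The same co-investigators also "conduct in-person fidelity check in 2% of randomly selected exercise sessions using a standard form".

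On who handles outcome scores, the Data audits section gives the principal investigator the audit of electronic outcome data. When the research assistant who collected the data and the one who entered it disagree, "the RAs need to consult the neuropsychologist co-investigator for correct scoring", and the resolved score goes into the database.

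On staff contact, the Staff training section says that staff, research assistants and volunteers receive ongoing training "through weekly staff meeting, monthly research team meeting, briefing after each treatment fidelity check", among other routes.

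**The concern.** The article claims a blinding property for investigators and then assigns some of them a duty that removes it. That would be a minor slip if investigators had no part in the outcome data, but they do: one co-investigator decides disputed scores and the principal investigator audits them. For these two roles the article offers no protection other than the sentence that the fidelity duty contradicts.

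The primary outcome gives this some weight. The ADAS-Cog is administered and scored by raters, with a quoted inter-rater reliability of 0.65 to 0.99, so at the lower end there is room for judgement. Participants know which exercise they do, so blinding can only be held on the assessment side. The primary test compares the cycling arm's mean 6-month change with a fixed external value of 3.2 points. In that test no concurrent arm can absorb a shift in scoring: any average shift in the cycling arm passes in full into the estimated difference from 3.2.

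**Working it through.** No power, alpha or sample size figure is in dispute, so the check sets the sections side by side and then counts the exposure.

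**Step 1. Does fidelity review reveal the arm?**
- What the reports hold: the section on exercise safety and adherence says the session forms record whether, and in what respect, the prescription was met. The section on participation in the exercise has heart rate and perceived exertion documented every 5 minutes.
- Cycling prescription (Cycling section, Table 2): 50 to 75% of heart rate reserve, or 9 to 14 on the Borg scale.
- Stretching prescription (Stretching exercise section, Table 2): at most 20% of heart rate reserve, or at most 8 on the Borg scale.
- The lowest cycling target exceeds the highest stretching target by 50 - 20 = 30 percentage points of heart rate reserve, or 9 - 8 = 1 Borg point. The ranges do not overlap, so a form that refers to the prescription identifies the arm. The review is also held with the person who led the session.

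**Step 2. Whose arm is revealed, and how often?**
- Planned subject-sessions: 90 x 72 = 6,480 (60 x 72 = 4,320 cycling; 30 x 72 = 2,160 stretching). All reports are reviewed, so the review covers all 90 subjects.
- In-person checks: 0.02 x 6,480 = 129.6, about 130 subject-sessions. If every session held the maximum of three subjects, that is 129.6 / 3 = 43.2, about 43 group sessions.
- Chance that a given subject is watched at least once, assuming independent selection of sessions: 1 - 0.98^72 = 0.77 with full attendance, 1 - 0.98^54 = 0.66 with 54 sessions, and 1 - 0.98^36 = 0.52 with 36.

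**Step 3. Can the two statements both be true?** The concealment statement covers all investigators but one. The fidelity section gives at least one other, the exercise physiologist, and by its plural wording more than one, knowledge of the arm. They cannot both hold if concealment means not knowing the assignment.

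**Step 4. Is the scoring side protected in another way?**
- Data collectors: yes, by separate statements. They are blinded (Design) and meet subjects only for data collection (Data collection).
- Neuropsychologist co-investigator and principal investigator: no separate statement. Their blinding rests on the blanket sentence alone, and no section says that someone who does fidelity review may not also audit or decide scores.
- Outcome-assessing research assistants: research assistants are among those trained through the briefing after each fidelity check, and no section limits what those briefings may reveal to them.

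**The case against.** The strongest reply is that the sentence may not describe a blind at all. The article tends to use concealment for investigators and blinding for assessors, and excepting the statistician would fit someone who holds the randomization list. Read that way, the sentence concerns only the next assignment before randomization, and the fidelity duty contradicts nothing. This is possible but fits poorly. The section heading covers blinding, and the very next sentence contrasts investigators with staff who are not blinded, which concerns knowledge of the assignment. If the narrow reading were right, the article would state no blinding at all for those who audit and decide scores.

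A second reply is that assessor safeguards are in place. That stands. Data collectors are blinded to group and to previous data, do not otherwise meet subjects, and have their work scored and entered by a second assessor. The control arm matches cycling on session length. None of this is disproved.

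Several stronger readings are tempting, and the article does not support them:
- *The score adjudicator or the principal investigator is unblinded.* No section places either in fidelity review. The example given there is the exercise physiologist, whereas disputed scores go to the neuropsychologist.
- *Early outcome data are checked by unblinded investigators.* The article says "The first five data collections will be double checked by co-investigators", but these may be baseline visits, which precede randomization.
- *The follow-up fitness tests are run by unblinded staff.* The staffing description that includes "a study staff/RA, and a physician co-investigator" concerns the screening test. Follow-up staffing is not stated.
- *Assessors hear individual subjects discussed.* The training section does not say so. It only fails to rule it out.

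**Conclusion.** The concern holds in a limited form. The statement that allocation is concealed from all investigators, or from all but the statistician, is wrong for every co-investigator who does fidelity review, and that review covers all 90 subjects. This rests on reading concealment as not knowing the assignment, which is the better reading of the section.

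For the scoring adjudicator and the principal investigator, the conclusion is that their blinding is unsecured, not that it is broken. The effect on the ADAS-Cog result cannot be sized: the article gives no rate of scoring discrepancies and no basis for how far expectation might move a resolved score. A reader might be inclined to express an assumed bias as a share of the 2.5-point target difference, but that would only restate the assumption. The point deserves correction because the outcome is rater-scored, the primary test has a fixed external comparator, and the remedy is cheap.

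**What to change.** 1. Correct the randomization and blinding section and the abstract together. Name the investigator roles that are unblinded through fidelity review, limit the concealment statement to the others, and treat the statistician the same way in both places.
2. State that anyone who reviews session case reports, attends exercise sessions or takes part in fidelity meetings may not check, audit or adjudicate ADAS-Cog or other outcome scores. This covers the neuropsychologist co-investigator and the principal investigator for as long as they hold the scoring and audit roles.
3. Keep outcome-assessing research assistants out of any part of the post-fidelity-check briefings that could reveal a subject's arm.

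The cost is a wording change, which under the Ethics section goes to the IRB and DSMB for approval, and slightly less freedom in assigning roles. No extra staff are needed, and the sample size and the exercise prescriptions are unaffected.
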